## Abstract

**Background:**

There is a need for effective population-based physical activity interventions. The internet provides a good platform to deliver physical activity interventions and reach large numbers of people at low cost. Personalised advice in web-based physical activity interventions has shown to improve engagement and behavioural outcomes, though it is unclear if the effectiveness of such interventions may further be improved when providing brief video-based coaching sessions with participants. The purpose of this study is to determine the effectiveness, in terms of engagement, retention, satisfaction and physical activity changes, of a web-based and computer-tailored physical activity intervention with and without the addition of a brief video-based coaching session in comparison to a control group.

**Methods/Design:**

Participants will be randomly assigned to one of three groups (tailoring + online video-coaching, tailoring-only and wait-list control). The tailoring + video-coaching participants will receive a computer-tailored web-based physical activity intervention (‘My Activity Coach’) with brief coaching sessions with a physical activity expert over an online video calling program (e.g. Skype). The tailoring-only participants will receive the intervention but not the counselling sessions. The primary time point’s for outcome assessment will be immediately post intervention (week 9). The secondary time points will be at 6 and 12 months post-baseline. The primary outcome, physical activity change, will be assessed via the Active Australia Questionnaire (AAQ). Secondary outcome measures include correlates of physical activity (mediators and moderators), quality of life (measured via the SF-12v2), participant satisfaction, engagement (using web-site user statistics) and study retention.

**Discussion:**

Study findings will inform researchers and practitioners about the feasibility and effectiveness of brief online video-coaching sessions in combination with computer-tailored physical activity advice. This may increase intervention effectiveness at an acceptable cost and will inform the development of future web-based physical activity interventions.

**Trial registration:**

ACTRN12614000339651**Date:** 31/03/2014.

## Background

Physical activity improves physical and mental health, and significantly lowers the risk of non-communicable disease including cardiovascular disease, diabetes mellitus and cancer [1]. It is estimated that individuals who are physically active have a 30% to 50% lower risk of non- communicable diseases and have a 20% to 50% lower risk of mortality than inactive individuals [2-4]. The World Health Organisation recommends 30 minutes of moderate intensity activity on 5 days of the week to receive health benefits and reduce the risk of non-communicable disease [5]. Despite this, more than 50% of Australians fail to meet these recommendations [6] which is estimated to cost the Australian economy 13.8 billion each year in healthcare, loss of productivity, and mortality costs [7]. Hence, there is an urgent need for effective physical activity interventions with a broad reach.

High levels of internet access (e.g. 83% in Australians) make the development and dissemination of web-based physical activity interventions worthwhile [8]. Health behaviour change interventions delivered via the internet have the potential to reach a large audience at low-cost, they are convenient for participants and enable the content to be delivered in a non-confrontational way [9-11]. Although the short-term effectiveness of web-based physical activity interventions is well-established, participant retention and engagement have been identified as a challenge with many web-based interventions reporting high dropout rates or low use of the websites after a period of time [12,13]. As the amount of exposure to the intervention content is strongly linked to behavioural outcomes, low participant retention and engagement may limit the effectiveness of web-based interventions [14,15].

Reviews have shown that successful web-based physical activity interventions have included personalised advice through coaching or computer-tailoring, numerous participant contacts, social support elements, and theoretically-based behaviour change techniques [13,16,17]. Randomised controlled trials have found that web-based interventions that provide some form of personalised advice result in improved engagement and behavioural outcomes compared to interventions providing generic advice [18,19]. Online coaching and computer-tailored advice are effective ways of providing personalised advice in web-based interventions that mimic the advice and support provided in traditional face-to-face counselling sessions, in a way that reduces geographical, time and cost limitations [18,20].

Coaching is defined as facilitating health behaviour change and improving health outcomes through interaction or partnership between a health professional (coach) and an individual client [21]. Online coaching sessions provide personal contact similar to traditional face-to-face counselling. Online coaching sessions are typically delivered through private messages (e-mail, SMS), real time instant messaging (chat) and group forums. Online coaching in web-based behaviour change settings has been found to improve perceptions of social support which is positively associated with behaviour change [22,23]. Counsellor initiated private messages and real time counselling sessions have been found to result in greater weight loss compared to web-based interventions providing information on weight loss only [24-27]. Other methods of delivering social support in web-based interventions with lower time and cost restraints include online peer discussions and provision of an available online coach (“Ask the expert” button). Neither method has been found to be successful at improving behavioural outcomes of the intervention, as few participants have shown to use these features [28]. Although the effectiveness of online coaching is well established, the high time and cost investment in comparison to computer-tailored advice means that they are rarely included in web-based health behaviour interventions aiming to reach a wide audience [29,30].

Computer-tailored advice is more common in web-based physical activity interventions as it can be delivered at a lower cost. Computer-tailored advice is automatically produced using a computer-based expert system that delivers feedback based on participant’s responses to a questionnaire [18]. Computer-tailored physical activity advice is read, printed, discussed and remembered more than generic advice [31]. Furthermore, it is also more appreciated by participants, processed more intently and leads to greater attention compared to generic advice [32]. As such, it is not surprising that it leads to improved health behaviour changes compared to generic health advice [33]. Despite the well-established effects of computer-tailoring, it is unknown if computer-tailored interventions would be more effective with an element of human support.

It appears no web-based physical activity interventions have provided both computer-tailored advice and online coaching simultaneously. It is therefore unknown whether this combined approach improves intervention outcomes. When computer-tailored advice is delivered prior to the online counselling session it can largely reduce the time required from a coach to provide feedback, therefore keeping the time and financial costs to conduct the intervention viable to reach large numbers. In addition the computer-tailored advice may reduce reliance on the knowledge and expertise of the coach. The addition of a brief online coaching session may add further explanation; personalisation and interpretation of the theory-based computer-tailored advice as well as provide a social support element [21,34,35]. Furthermore, advances in internet technology and broadband capacity allow the coaching sessions to be delivered via free online video-calling programs (e.g. Skype) which, unlike online instant messaging or forums, enables the participant to view the coach whilst engaging in a verbal discussion. Psychological counselling over video calling programs is becoming widely used and accepted [36]. Video-coaching facilitates higher engagement, feelings of accountability and social support, and reduces the risk of misunderstandings compared to emails and instant messaging [36,37].

The current study will examine the feasibility, engagement, retention and effectiveness of a computer-tailored web-based physical activity intervention, with and without brief online video-coaching sessions. The findings will guide health promotion professionals in delivering future large-scale web-based physical activity interventions that are effective at engaging participants and producing long-term behaviour changes. More specifically this study will assess the between group differences in physical activity outcomes as a result of receiving computer-tailored advice inclusive of video-counselling sessions, compared to computer-tailored advice alone and a wait-list control group. The secondary analyses will assess between group differences in website engagement (website user statistics and fidelity), retention, participant satisfaction, quality of life, and correlates of physical activity (mediators and moderators). The fidelity and satisfaction with the video-coaching sessions will also be measured to assess the feasibility of this intervention approach.

## Methods/Design

### Participants

Participants will be eligible to participate if they are English speaking adults (over 18 years) who reside in Australia, and do not meet the physical activity recommendations. Participants will need to have an internet connection and a computer processing system efficient enough to watch videos online, in order for an online video-calling program (such as Skype, Google Hang Out or Face Time) to work effectively. Participants will be excluded if they are: non- English speaking, pregnant, under 18 years of age, currently meeting the Australian physical activity guidelines (assessed by a single item, ‘do you currently participate in less than 30 minutes of physical activity on average each day?’), or at risk of injury or ill health from increasing their physical activity (assessed by the Physical Activity Readiness Questionnaire [38]).

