#### Physical activity

The validated Active Australia Questionnaire will be used to measure total physical activity and whether participants meet the physical activity guidelines [53]. This tool assesses the number of sessions and total time spent walking, participating in moderate physical activities, vigorous physical activities and gardening during the previous week. Total physical activity time is calculated by summing the time spent walking, performing moderate-intensity physical activity, and performing vigorous-intensity physical activity multiplied by two. Physical activity sessions need be 10 minutes or longer to be included. Participants are categorized as being sufficiently physically active for health benefits if they participated in a minimum of 150 minutes of physical activity per week. The Active Australia Questionnaire has been found to have a good test-retest reliability (Kappa = .52) [54], a high percentage agreement with other physical activity measures (67%-75%) [55] and is sensitive enough to detect changes in physical activity [14].

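### The telephone screening item cuts at 210 min/week, but the protocol puts meeting the guidelines at 150 min/week, so people the exclusion is meant to remove can be enrolled

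*Protocol article*

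**What the plan says.** The Participants section of the protocol article limits entry to adults who "do not meet the physical activity recommendations". It excludes those "currently meeting the Australian physical activity guidelines (assessed by a single item", and that item reads "do you currently participate in less than 30 minutes of physical activity on average each day". Under Recruitment, a researcher judges eligibility by telephone, and eligible callers are then randomised. No later activity check is described. The AAQ is part of the baseline questionnaire but is not used as a screen.

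The Physical activity subsection of Measures says that the AAQ "will be used to measure total physical activity and whether participants meet the physical activity guidelines", and classes a participant as "sufficiently physically active for health benefits if they participated in a minimum of 150 minutes of physical activity per week". The AAQ total adds walking, moderate and vigorous time, with the last term given as "performing vigorous-intensity physical activity multiplied by two". Only sessions of 10 minutes or more count. The Background says that the World Health Organisation "recommends 30 minutes of moderate intensity activity on 5 days of the week".

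**The concern.** Eligibility and outcome measurement refer to the same concept, meeting the guidelines, but apply different rules to it. The screen is a daily average with no intensity, session length or weighting. The outcome rule is a weekly total with all three. If the screening cut-off is higher than the outcome threshold, the exclusion does not do what it says: some participants start the trial already on the far side of the line it draws.

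Two things are at stake. One is the description of the population to whom the result applies. The other is the meaning of the guideline-attainment classification, because anyone who starts at or above 150 AAQ minutes can keep or lose that status but cannot newly gain it.

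**Working it through.** **Inputs, all from the protocol article**
- Screening cut-off: 30 min/day on average (Participants).
- Sufficient activity: at least 150 min/week on the AAQ, vigorous time doubled, sessions of at least 10 minutes (Measures, Physical activity).
- Recommendation: 30 minutes on 5 days (Background).

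**Reproducing the protocol's own threshold.** 30 × 5 = 150 min/week. The Background and the AAQ rule agree.

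**Converting the screening item.** 30 × 7 = 210 min/week. The gap is 210 − 150 = 60 min/week, and 60/150 = 40%. With no vigorous activity, the daily average that corresponds to the AAQ threshold is 150/7 = 21.4 minutes, not 30.

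**Putting the two rules side by side.** Let w, m and v be weekly minutes of walking, moderate and vigorous activity in sessions of at least 10 minutes. Let u be other activity that a caller might count but the AAQ total does not (light activity, gardening, short sessions).
- The screen admits if w + m + v + u < 210.
- The AAQ classes as sufficient if w + m + 2v ≥ 150.

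Both can be true at once, and both can be false at once:
- w = 150 (30 minutes on 5 days): 21.4 min/day, admitted; AAQ 150, sufficient.
- w = 209: 29.9 min/day, admitted; AAQ 209, sufficient.
- v = 75: 75/7 = 10.7 min/day, admitted; AAQ 2 × 75 = 150, sufficient.
- u = 210 and nothing else: 30 min/day, excluded; AAQ 0, not sufficient.

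**How many might be affected.** The protocol gives no activity distribution, so this is illustration only. Assume that weekly minutes follow a gamma distribution F, that callers answer exactly, and that there is no vigorous activity. The share of those passing the screen who are already at 150 or more is [F(210) − F(150)] / F(210).
- Mean 100, SD 100: (0.8775 − 0.7769) / 0.8775 = 11.5%.
- Mean 150, SD 120: 20.3%.
- Mean 180, SD 150: 22.2%.
- Mean 200, SD 200: 18.8%.
- Mean 250, SD 250: 20.6%.

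Under these assumptions the share is about 12% to 22%, or 12 to 22 of the planned 100 per arm. Doubling vigorous minutes would raise it. Callers who count activity that the AAQ leaves out would lower it.

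**The case against.** The strongest reply is that this is a rough telephone screen and little depends on it. Much of that stands.

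- **Bias.** A reader might infer that the comparison between arms is compromised. It is not: the same item is put to everyone before randomisation, and baseline is a time point in the mixed model.
- **Dilution.** A reader might infer that the treatment effect shrinks in proportion to the share already active. The documents do not support this. The primary outcome is change in physical activity, which the Statistical analyses section models with a linear mixed model, and AAQ minutes have no ceiling at 150. No analysis of newly meeting the guideline is described. Participants who start above 150 can also relapse, which Module 4 addresses, so they can still contribute to a difference in attainment.
- **Direction.** Because the item names no intensity, it can err both ways, and the net misclassification cannot be worked out from the document.
- **Daily target.** The Module 3 description mentions scheduling 30 minutes every day, and the feedback graph shows both a minimum and an optimal recommendation, so the item may reflect a daily standard. The text of the Australian guidelines is not reproduced. However, nowhere does the protocol define meeting the guidelines as 210 min/week, whereas it gives 150 under Measures and an equivalent in the Background. If a daily standard was intended, the sections still need reconciling.

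Condensation into an article is no answer here. The item and the threshold are both printed, and they disagree.

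**Conclusion.** The point holds as a mismatch between the eligibility criterion and the question used to apply it. A literal, truthful answer admits people at 150 to 209 min/week, and people with as little as 75 vigorous minutes, whom the trial's own AAQ rule classes as sufficiently active. It can also turn away people whose activity is only light. The 60 min/week gap follows from the protocol's figures alone. The number affected does not: such people can be enrolled, but the document does not show how many will be, and the 12% to 22% above rests on assumed distributions.

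The consequence is limited to the description of the enrolled population and the interpretation of guideline attainment. It would also go too far to say that the trial meant to enrol inactive adults: the criterion is not meeting the recommendations, which is a weaker condition. This is worth correcting because it is cheap and cannot be undone after enrolment, but it does not threaten the validity of the primary comparison.

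**What to change.** Choose one definition and use it in both places.

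1. Either align the telephone item with the AAQ rule, so that a caller is eligible if walking + moderate + 2 × vigorous minutes, in sessions of at least 10 minutes, total less than 150 in the week; asking the AAQ items on the call does this directly. Or keep the present item and restate the criterion as what it measures, an average below 30 minutes a day of self-defined activity.
2. Report, by arm, the share at or above 150 AAQ minutes at baseline. This is useful even after option one: the AAQ covers a single week and its stated test-retest kappa is .52, so some people will cross the line between screening and baseline.
3. In any analysis of guideline attainment, account for baseline status.

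Simply replacing 30 minutes a day with 150 minutes a week in the question would not be enough. A caller with 80 vigorous minutes would still pass and then score 2 × 80 = 160.

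Cost: a slightly longer screening call and slightly fewer eligible callers, so recruitment may be a little slower. Restating the criterion instead costs only an edit. The baseline report uses data already being collected.

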### Recruitment

Print and internet advertising will be used to recruit participants. Print advertising will include newspaper advertising in newspapers and posters and leaflets promoting the intervention will displayed in sporting clubs, schools, the university and medical centres. The internet advertising will include free posts on community websites, and Google and Facebook advertisements. All advertisements will direct interested individuals to a specific recruitment page that is part of the intervention website where they can find out more information about the study and download the participant information sheet. If they are interested in registering, individuals will be asked for their contact details and to give their consent to participate via an online consent form. A researcher will then call participants via telephone to assess their eligibility. Participants who are eligible will be randomly assigned to one of the three groups and notified of their log-in details and intervention starting date. Participants will be allocated at random using a computer generated sequence. Group assignment will only be disclosed after participants have completed the baseline assessment.

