### Procedure

Participants will be randomly assigned to one of three groups, tailoring + video-coaching, tailoring-only or wait-list control. All tailoring groups will receive a web-based physical activity intervention named ‘*My Activity Coach*’ that consists of 4 modules of computer-tailored advice. Additionally the tailoring + video-coaching participants will also receive 4 brief coaching sessions with a physical activity expert to discuss the personalised advice they received in the previous module. To control for exposure to additional intervention contacts in the tailoring + video-coaching groups the tailoring-only participants will receive a total of 4 tailored emails to remind them of the tailored advice they received in the previous module, but they will not receive any coaching. Questionnaire data will be collected at baseline, immediately post-intervention at week 9, and 6 and 12 months post baseline (see Figure 1). All questionnaires will be completed through the intervention website, including the waitlist control group (though no tailored content will be available for these participants). Satisfaction with the intervention will only be measured at 9 weeks in intervention group participants. Participant retention, engagement, and feasibility of the coaching sessions will be measured for the intervention participants throughout the intervention. Participants in the wait-list control group will be given the opportunity to participate in the intervention after they have completed the 12-month follow-up questionnaire (see Figure 1). The research has been approved by the Central Queensland University Human Ethics Committee (H13/04-044), and complies to the Helsinki Declaration.

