### Statistical analyses

#### Intervention effects

Data will be analysed using intention-to-treat principles. Physical activity will be modelled using the using linear mixed models with random intercepts, the fixed effects of group (control, tailoring only, tailoring + video-coaching) and time (baseline, post-intervention, 6-months, 12-months), and a group by time interaction and will adjust for potential confounders including gender, age, education, income, employment, location, marital status and BMI if they are associated with physical activity and time.

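### Randomisation and the start-date notice come before the website baseline: people lost in between are randomised without data, and an arm-specific date could reveal the wait-list arm

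*Protocol article*

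**What the plan says.** All places are in the protocol article.

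- **Recruitment**, directly after the eligibility telephone call: eligible people are to be "randomly assigned to one of the three groups and notified of their log-in details and intervention starting date".
- **Recruitment**, last sentence: "Group assignment will only be disclosed after participants have completed the baseline assessment".
- **Procedure**, on where questionnaires are filled in: "All questionnaires will be completed through the intervention website, including the waitlist control group".
- **Procedure**, on wait-list access: "Participants in the wait-list control group will be given the opportunity to participate in the intervention after they have completed the 12-month follow-up questionnaire".
- **Demographics**: the demographic variables are collected in the baseline survey. Measures confirms that they are asked only then.
- **Intervention effects**: "Data will be analysed using intention-to-treat principles". The linear mixed model has fixed effects of group and "time (baseline, post-intervention, 6-months, 12-months), and a group by time interaction", with adjustment for demographic variables that meet a stated association criterion.
- **Sample size**: 100 per arm, effect size 0.43, alpha 0.05, 80% power, 25% attrition.

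**The concern.** The order of events leaves a gap between randomisation and the first data collected under it. Someone who passes the telephone screen, is randomised and then never opens the website belongs to the intention-to-treat population but has no activity score at any time point and no demographic covariates. A mixed model uses whatever observations a participant has; with none, it cannot include that person. The Background describes high dropout and low website use as known problems of web-based interventions, so such early losses are foreseeable.

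The second issue is what the notice contains. For a wait-list participant, a true start date is about a year away. If that date arrives with the log-in details, the participant can work out the allocation before giving the baseline answers. This matters because the primary outcome is change in self-reported activity, so baseline forms part of it.

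**Working it through.** **1. Order of events.** Recruitment goes from eligibility call to random assignment to notice of log-in details and start date. Procedure puts every questionnaire on the website, so the log-in must precede baseline. The rule that assignment is disclosed only after baseline fits this order: there is something to withhold only if the allocation already exists. As written, allocation precedes baseline.

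**2. What the start date could reveal.** There are two possibilities.
- The date is specific to the arm. The wait-list date then falls after month 12 (Procedure), the notice identifies the arm, and the disclosure rule is broken.
- The date is common to all arms. Nothing is revealed, but for the wait-list third the date is not when they start the intervention.

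The article does not say which applies. Either way the wording needs reconciling.

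**3. The stated sample size.** Inputs from Sample size: effect size d = 0.43, alpha 0.05 (taken as two-sided; not stated), 80% power, 25% attrition.
- Simple two-group comparison: n = 2(1.960 + 0.842)² / 0.43² = 84.9, so 85 evaluable per arm. With attrition, 84.9 / 0.75 = 113.2, so 114.
- With baseline adjustment, n is multiplied by (1 − ρ²). At ρ = 0.35: 84.9 × 0.8775 = 74.5, and 74.5 / 0.75 = 99.3, so 100.

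The article gives no ρ. The stated 100 per arm is compatible with a correlation near 0.35 and is not disputed here.

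**4. Effect of loss before baseline.** Let m be the share of randomised people lost before baseline. The article gives no value, so 5%, 10% and 20% are assumptions, applied on top of the 25%.
- Evaluable per arm: n = 100 × (1 − m) × 0.75.
- Power: Φ(d√(n/2) − 1.960). With baseline adjustment at an assumed ρ = 0.34, replace d by 0.43/√(1 − 0.34²) = 0.457.

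| m | n per arm | Power, unadjusted | Power, ρ = 0.34 |
|---|---|---|---|
| 0 | 75 | 75.0% | 80.0% |
| 5% | 71.25 | 72.8% | 77.9% |
| 10% | 67.5 | 70.5% | 75.7% |
| 20% | 60 | 65.4% | 70.7% |

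The fall between m = 5% and m = 20% is 2.2 to 9.6 points unadjusted and 2.1 to 9.3 points adjusted. The noncentral t gives 74.4%, 72.2% and 64.7% at n = 75, 71.25 and 60, a fall of 2.2 to 9.7 points. Only the fall from the m = 0 row belongs to this point; the gap between 75% and 80% in that row has nothing to do with the timing of randomisation. If the 25% already includes people lost before baseline, the m = 0 row applies and there is no loss.

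**5. Equivalent in recruitment.** To have 100 per arm at baseline under the present order, 100/0.95 = 105.3 (106) to 100/0.80 = 125 per arm would have to be randomised.

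**The case against.** A reader might infer that the notice reveals wait-list allocation and so biases baseline reporting between arms. The article does not support that. It states that assignment is withheld until baseline is complete, and only an arm-specific date would defeat this. Sending log-in details to everyone is uninformative, since the wait-list group also uses the website. If concealment works as stated, failure to complete baseline cannot depend on the participant's knowledge of their group, so what is expected is lost precision rather than differential bias. No size can be put on such a bias from the documents. This part of the objection stands.

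It is also fair to say that the loss rates have no source in the article, that the 25% may already include them, that the trial was sized for a mixed model rather than a two-sample test, and that randomising first with disclosure withheld is a workable order. Handling of randomised people with no data may be set out in the full protocol or analysis plan, and Figure 1, whose content could not be read in the text at hand, may show the timing.

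None of this changes the written order. Randomisation before baseline is a stated choice, it allows loss after randomisation and before any data, and the start-date wording can be read in a way that conflicts with the disclosure sentence.

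**Conclusion.** The point holds in a limited form. As written, allocation and the start-date notice precede the website baseline, so a person who never logs on is randomised yet contributes nothing to the intention-to-treat model. Someone who skipped baseline but answered later questionnaires would still lack the baseline score and the covariates. Possible unmasking of the wait-list arm depends on an arm-specific date and is an ambiguity to resolve, not an established breach.

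The size is about 2 to 10 points of power at d = 0.43. This assumes 5% to 20% loss before baseline in addition to the 25% attrition, a two-sided alpha of 0.05, and 100 randomised per arm. It is zero if the 25% already covers that loss. The change is worth making because it is cheap and cannot be applied once participants have been randomised.

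**What to change.** Reorder the steps in Recruitment:

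1. After the eligibility call, send log-in details only.
2. Have the website draw the next allocation from the computer-generated sequence when the baseline questionnaire is submitted.
3. Then disclose the group and the start date.
4. State in Sample size that the 300 are participants randomised after completing baseline.

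This removes loss between randomisation and baseline, and any risk that the date reveals the arm before baseline. The cost is a minor reordering of the website workflow, start dates scheduled after baseline rather than at the call, and a small text change; no visits or staff are added. More people may need to be screened to reach 300, but those who drop out before baseline would no longer count as randomised.

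If the present order has to stay, state that the notified date is the same for all arms and what it refers to, and state whether the 25% includes people lost before baseline.
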